### 2.6. Outcome measures

Testing is completed at baseline (Week 0) and within 7–10 days of intervention completion (maximum 16 weeks). (**Fig 1**) All measures are collected at all time points unless specified below. Baseline testing is performed before randomization. Patients are provided with monetary compensation for each testing timepoint attended, and parking validation for every visit to DFCI.

**Fig 1 pone.0322192.g001:**
[figure not shown]
Spirit study timeline and data collection time points.

#### 2.6.1. Primary outcome.

*2.6.1.1. Feasibility*

Feasibility of the RE intervention The intervention is considered feasible if 1) patients attend ≥70% of the total prescribed number of exercise sessions (dependent on their treatment duration) [17,32] and 2) **≥**70% of sessions completed at the planned prescription (i.e., relative dose intensity ≥ 100%). The planned exercise volume (sets x reps x weight) is established prior to exercise session with the %1RM weights calculated from 10RM testing at baseline. However, in the event estimated 1RM is not available or the patient is not being adequately progressed during the intervention (i.e., weights become to easy to move relative to intended %1RM intensity), the lead exercise trainer would prescribe the highest tolerable weight based on pre-determined volume (sets x repetitions). A dose modification is defined as a reduction in sets, repetitions, and/or weight during the session that deviated from the planned volume, whereas a dose escalation is defined as an increase in sets, repetitions, and/or weight. Both dose modification and escalation were applied during the session at the discretion of the exercise trainer and reported as actual volume completed. Planned and actual volume for each resistance exercise were respectively calculated and summed to derive total planned and actual prescribed volume for each session, which were summed to obtain total planned and actual intervention volume. Exercise relative dose intensity is then calculated as the ratio of total actual resistance volume to total planned resistance volume. Reasons for missed sessions are documented throughout the study. [33] To account for missed sessions due to illness, family and work obligations, patients are given 6 exercise sessions to make-up at the end of their program if their treatment timeline permits. Feasibility of the RE ± PS intervention: The same criteria described above are used for the exercise portion. Additionally, patients are considered compliant and the PS intervention feasible if they consume ≥70% of the total prescribed doses of protein supplementation. Protein adherence is captured for the RE + PS group by asking patients during the supervised exercise sessions if they have been compliant with protein supplementation intake and recording on the exercise sessions data sheet.

#### 2.6.2. Secondary outcomes.

*2.6.2.1. Skeletal muscle mass*

Skeletal muscle mass is examined by standard-of-care CT scans. Skeletal muscle area is measured on axial CT images at the level of the L3 vertebral body using a validated, fully automated algorithm. [34] Skeletal muscle index (SMI) is calculated as the ratio of muscle area (cm^2^) to squared height (m^2^). This fully automated method estimates a patient’s body composition from an abdominal CT scan and has been validated across two large scale and diverse datasets. [35,36] Sarcopenia will be defined as index SMI < 38.5 cm^2^/m^2^ for women and < 52.4 cm^2^/m^2^ for men. [37]

*2.6.2.2. Cachexia-related blood biomarkers*

Fasting (12 hour fast) blood is drawn by a trained phlebotomist. For each patient, two 10 ml tubes are collected into EDTA and Serum tubes, along with one additional lavender topped tube (whole blood in EDTA). Samples are centrifuged and then aliquoted and stored at -80 degree C at DFCI for future measures. Blood samples are transported to the [name] lab for storage and batch-testing of plasma biomarkers occurs at DFCI for IL-6, MCP-1, TNF-RII, and branched chain amino acids by ELISA, and liquid chromatography tandem mass spectrometry.

#### 2.6.3. Tertiary outcomes.

*2.6.3.1. Anthropometrics*

BMI (kg/m^2^) is calculated from height and weight. A tape measure is used to obtain waist and hip circumference defined as the distance around the smallest part around the waist between the 12^th^ rib and iliac crest and the widest girth of the buttocks using the greater trochanter as a landmark, respectively. Body composition is assessed via bioelectrical impedance using a validated device (Tanita 780, Arlington Heights, IL).

*2.6.3.2. Muscular strength*

Upper body and lower body strength is measured using the 10-repetition maximum (10-RM) test using a machine chest press and leg press respectively using validated equations to calculate estimated 1-RM. [38,39] Following a warm-up, patients are given 5 attempts to reach the final 10-RM load with a 1–2-minute rest period between attempts. The 10-RM method has been validated in cancer populations with high to very high reliability. [40] Furthermore, for those randomized to the exercise group, the 1-RM is estimated from 10-RM muscle strength tests on the 6 exercises prescribed in the intervention to determinate exercise prescription: 1) chair squat, 2) chest press, 3) glute bridge, 4) row, 5) lunges, 6) shoulder press. Hand grip strength is measured using a hand-held dynamometer on the patient’s dominant hand. The subject is asked to grip the handle of the dynamometer with one hand using as much grip pressure as possible while holding for 5 seconds. The subject is asked to complete 3 grip strength attempts.

*2.6.3.3. Cardiorespiratory fitness*

Cardiorespiratory fitness is assessed by the 6-minute walk test (6MWT), a validated test in cancer survivors. [41] Patients are instructed to walk as quickly as possible without running on an indoor pre-measured walkway for 6 minutes. Distance achieved in 6 minutes is measured in meters.

*2.6.3.4. Blood pressure and resting heart rate*

Blood pressure (BP) and resting heart rate (HR) are measured using an automated device with an appropriately sized cuff (Omron BP 786, Lake Forest, IL) after the patient has sat quietly for 5 minutes while resting their arm on a table so the brachial artery is level with the heart.

*2.6.3.5. Physical function*

The short physical performance battery (SPPB) [42] includes three sections: 1) balance with feet together, semi tandem, and full tandem is held for up to 10 seconds (s) with no support; 2) usual gait speed over 4m is timed with two attempts given and the fastest time is recorded; and 3) the five-chair stand test is performed where the time to complete five chair sit-to-stands is recorded. A score is given for each section of the SPPB and a total summary score. The timed up and go (TUG) [43] test times how fast a patient could stand up from a chair, walk around a cone placed 3m away, and end in a seated position. Gait speed [44] over a 6m flat surface is assessed and the time to talk the course at a usual pace and a fast pace is recorded with two attempts given for each speed. The Margaria stair climb [45] is completed in a stairwell of ten stairs. Patients walk or run up the stairs as fast as they can. The time the patient takes from stair three to stair nine is recorded, with three attempts given after a familiarization practice, and the fastest time is used. Power is calculated from the stair climb using a validated equation. [45] The sit-to-stand [46] test times how many sit-to-stands a patient can perform in 30s from a seated chair position to a standing position with full hip extension. Only one attempt is given and the number of repetitions with correct technique are recorded.

*2.6.3.6. Patient-reported outcomes*

Health-related quality of life (QOL) is assessed using the FACT-Hep (Functional Assessment of Cancer Therapy-Hepatobiliary), a hepatobiliary (liver, bile duct, pancreas) cancer-specific questionnaire comprised of 45 items to specifically assess quality of life. [47] The Brief Fatigue Inventory (BFI) is used to rapidly assess the severity and impact of cancer-related fatigue including six items that correlate with QOL measures. [48] Depressive symptoms are assessed using the 20-item Center for Epidemiologic Studies Depression (CES-D) scale, which was designed to measure the individual’s current level of depressive state. [49,50] Sleep quality is assessed using the Pittsburg Sleep Quality Index (PSQI) which contains 19 questions evaluating seven domains of sleep: subjective sleep quality, sleep latency, sleep duration, habitual sleep efficiency, sleep disturbances, use of sleep medication, and daytime dysfunction. [51,52] The Brief Pain Inventory – short form (BPI) is used to assess the impact of pain on QOL. The BPI includes a sensory and reactive dimension and has been previously validated in breast cancer survivors. [53,54] Barriers to recruitment and exercise adherence are assessed using the 17-item Barriers to Recruitment Participation Questionnaire (BRPQ), [55] and the 43-item Exercise Benefits/Barriers Scale (EBBS). [56] Participant burden is assessed using the 21-item, Perceived Research Burden Assessment (PRBA). [57] Physical function is assessed using the Patient Reported Outcome Measure Information System (PROMIS) Physical Function-10 scale. [58]

2.6.4.Covariates and other measures

*2.6.4.1.Sociodemographic and clinical information*

Sociodemographic are collected using a set of questions self-reported by patients and extracted from medical records. Medical and surgical history is obtained from the treating physician providing clearance to participate in the trial.

*2.6.4.2.Dietary assessment*

Automated self-administered 24-hour dietary assessment tool are used to assess recent dietary patterns for two weekdays and one weekend day, recording all food and drink consumed during the previous 24-hour period. [59] Patients’ consumption of macro- and micronutrients is analyzed.

*2.6.4.3.Physical activity assessment*

Patients are provided with an accelerometer (ActiGraph, Pensacola, FL) to wear for seven days at every testing visit and are instructed to wear the water-resistant accelerometer at all times except for when swimming, showering, and sleeping. The device is provided to the patients, along with instructions of use and postage to return to the study staff after the seven-day period.

**2.6.5. Measures taken during intervention**

*2.6.5.1.Physical activity log and protein supplementation log*

During the exercise sessions, those in exercise groups are asked about any physical activity completed since the last supervised exercise session. Their response is recorded on the exercise session data collection sheet. The AC group completes daily physical activity logs throughout the intervention period. Additionally, those in the resistance exercise and protein supplementation group are asked about the consumption of the protein supplement since last supervised session with whether they did or did not take it. This is also noted on the exercise data collection sheet.

*2.6.5.2.Safety considerations: Questionnaires completed during the exercise sessions*

Exercise tolerance is recorded using the Exercise-Induced Feeling Inventory (EIF). This inventory assesses the individual’s feeling state change(s) post-exercise and is also used for the assessment of self-motivation to adhere to the resistance exercise regimen. [60] Patients are asked to complete the inventory before and after each exercise session. Therapy-related symptom checklist (TRSC) is used to assess and identify patient-reported symptom occurrence and severity each visit for the exercise groups. TRSC contains a 25-item checklist, with response choices ranging from “0” (none) to “4”(very severe). Any symptoms identified as “Severe” or “Very Severe” are discussed with the patient, with potential actions including: no exercise, reduced intensity, removal of an exercise, or an alternative exercise incorporated.

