### 2.5. Intervention

#### 2.5.1. Exercise intervention.

*2.5.1.1. Resistance exercise group (RE):*

The exercise intervention is home-based virtually supervised via Zoom. Patients complete three sessions per week for the duration of their neoadjuvant chemotherapy treatment with a maximum intervention duration of 16 weeks. The RE prescription consists of 2–3 sets of 8–12 repetitions at 70–85% estimated one-repetition maximum (1-RM) and/or at a rate of perceived exertion (RPE) of 6–7 on the Borg 10-scale. Session duration is approximately 60 minutes. Planned prescribed weight was calculated as a percent of estimated 1RM, which was tested at baseline via 10RM for each exercise. Initially, the weight was set at 70% of 1RM and increased by 5% every 2 weeks until week 8, reaching 85% of 1RM. From week 9 to 16, the prescribed weight increased where the highest tolerable weight for the intended repetitions and sets was used to gradually progress the weight. In the event a patient was not able to follow a linear progression due to injury or treatment-related side effects, the highest tolerable weight for the intended repetitions and sets was used. Exercises include chair squat, floor chest press, glute bridge, seated bent over row, lunges, and shoulder press. Exercises are tailored to the patients where the use of alternative exercises targeting similar muscle groups are incorporated depending on the health and physical status of the patients. Each exercise session begins with a 5-minute functional movement-based warm up and culminates with 5 minutes of stretching and 2 core exercises. Patients randomized to this group are provided with handheld weight-adjustable dumbbells and resistance bands. Patients keep all the exercise equipment after the intervention. Furthermore, an automated blood pressure cuff may be provided if study staff deem it necessary for patients’ safety.

*2.5.1.2. Resistance exercise combined with protein supplementation group (RE + PS):*

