The same RE intervention described above is prescribed to the RE + PS group. Patients additionally receive and are asked to consume 40g per day of protein (Unjury, Middletown, CT) equating to 2 scoops of protein supplement, [25] aiming to increase their overall protein intake to 1.2–1.5 g/kg of ideal body weight per day, to align with the current protein intake guidelines for adults with chronic diseases and to maximize stimulation of skeletal muscle protein synthesis. [26] On the day of exercise (3 days per week) the patients are asked to consume the protein supplement immediately (within 30 minutes) after exercise. This has been reported as the optimum time to consume protein to enhance muscle protein synthesis. [21,27,28] Timing of protein supplementation intake on non-exercising days (4 days per week) is not dictated, although patients are recommended to consume the 40g dose with a meal, or over two meals (e.g., 20g at breakfast and 20g at lunch), and record time(s) of day consumed. [29] Patients are provided the protein supplement and a shaker bottle with recommendations on how the protein supplement may be prepared and consumed (e.g. with water, milk.).

*2.5.1.3. Attention control group*

This group performs a home-based program of the same stretches utilized in the two intervention groups. The stretching protocol consists of one set of 3–4 static stretching exercises held for 30 seconds and performed 3 days/week. As flexibility exercises are low intensity, low impact and low-volume, minimal caloric expenditure is expected to be incurred. To increase compliance [30] and aid in the standardization of the home-based stretching, [31] patients are provided a booklet of the flexibility exercises. Patients are shown how to use the booklet and instructed in the stretching exercises by study staff prior to the intervention. In addition, patients are asked to complete weekly records of flexibility compliance and physical activity performed outside the study. This group is offered the RE + PS intervention after their treatment period and may start anytime within and up to a time of 6 months post-surgery date. Given the intervention length is dictated by treatment, we offer an intervention that matches the length of the neoadjuvant chemotherapy regime they received during the initial intervention period up to a maximum of 16 weeks. Patients are offered the choice of daily protein supplement if they elect to partake in the RE intervention.

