### 2.7. Adverse events

Adverse events (AEs) will be reported and graded according to the revised NCI Common Terminology Criteria for Adverse Events (CTCAE) version 5.0. Investigators must promptly notify the Principal Investigator (PI) of any unanticipated problems or life-threatening complications. Any adverse events occurring after the initial dose of study treatment, during treatment, or within 30 days of the last dose, must be reported to the PI using the local institutional SAE form. All expected and unexpected AEs will be communicated to the PI, who will then report them to the institutional review board. Serious adverse events must be reported within 24 hours of occurrence or discovery. All adverse events, both serious and non-serious, along with any deaths occurring during the study initiation, intervention, and within 30 days of the last study intervention, will be monitored until resolution, stabilization, or until the investigator determines the event to be irreversible, or the participant is lost to follow-up. Adverse events will be documented in the participant’s medical records and the appropriate case report forms. Given the remote nature of the exercise sessions, additional safety measures include providing specific exercise and assessment recommendations (e.g., standing near a wall for balance activities), adapting exercise protocols as needed (e.g., limiting weight or modifying resistance exercises), verifying participants’ home addresses to enable emergency response, and ensuring up-to-date emergency contact information is available for all participants.

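### Symptoms are asked about at every supervised session in the exercise arms, but no interim query is described for controls, so a by-arm reading of adverse events may be biased against exercise

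*Protocol article*

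**What the plan says.** **Exercise arms (RE and RE + PS).** Section 2.5.1.1 sets the contact schedule: "Patients complete three sessions per week for the duration of their neoadjuvant chemotherapy treatment with a maximum intervention duration of 16 weeks". Section 2.6.5.2, on safety, places two instruments around those contacts. For the Exercise-Induced Feeling Inventory, "Patients are asked to complete the inventory before and after each exercise session". The therapy-related symptom checklist (TRSC) covers "patient-reported symptom occurrence and severity each visit for the exercise groups", and "TRSC contains a 25-item checklist" scored from 0 to 4. Answers of severe or very severe "are discussed with the patient, with potential actions including: no exercise, reduced intensity, removal of an exercise", or a substitute exercise.

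**Control arm.** Section 2.5.1.3 describes stretching at home from a booklet, and "patients are asked to complete weekly records of flexibility compliance and physical activity performed outside the study". Section 2.6.5.1 adds: "The AC group completes daily physical activity logs throughout the intervention period". Neither section mentions a symptom item.

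**All arms.** Section 2.7 grades adverse events by CTCAE version 5.0 and follows up "All adverse events, both serious and non-serious, along with any deaths occurring during the study initiation, intervention" and the 30 days after the last study intervention. It requires events to reach the principal investigator and to be entered in medical records and case report forms. It sets no limit by arm and no common way or schedule of asking. Sections 2.6 and 2.6.3.6 give every arm quality-of-life, fatigue, depression, sleep and pain scales at baseline and at the end of the intervention. Section 2.4 says that patients, interventionists and outcome assessors are not blinded.

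**The concern.** All three arms receive neoadjuvant chemotherapy, so many symptoms will be treatment effects that occur in every arm. The control arm is what would let a reader separate these from effects of exercise. That works only if events have a similar chance of being found on each side. Here one side is asked through a structured list at each live contact with staff. For the other side, no symptom query is described between the two testing visits.

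A safety table by arm is a natural product of a randomised pilot that grades adverse events, and the introduction presents resistance exercise and protein supplementation as safe. If the table shows more events under exercise, nobody could tell a real excess from better detection. A later efficacy trial might then inherit a false safety signal.

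**Working it through.** The article states no figure on this point, so there is none to reproduce. The check counts the contacts and then asks what unequal capture would do.

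**1. Scheduled symptom checklists per patient** (sections 2.5.1.1 and 2.6.5.2)
- Exercise arms: 3 sessions per week × 16 weeks = at most 48 checklists; 48 × 25 items = at most 1,200 item queries. This is a ceiling, because the duration follows the chemotherapy.
- Control arm: none described.

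**2. Expected ratio when the true incidence is equal.** Let *t* be the true incidence in every arm, *cE* the share captured in the exercise arms and *cC* the share captured in controls. The apparent ratio is (*t* × *cE*) / (*t* × *cC*) = *cE* / *cC*, so *t* cancels. The article gives no capture rates; those below are assumptions.

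| Assumed *cE* | Assumed *cC* | Apparent ratio |
|---|---|---|
| 0.95 | 0.95 | 1.00 |
| 0.95 | 0.80 | 1.19 |
| 0.95 | 0.60 | 1.58 |
| 0.95 | 0.40 | 2.38 |

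**3. How often a false excess would appear at this sample size.** Inputs: 30 exercise and 15 control patients (section 2.9); equal true per-patient probability of an adverse event, assumed 0.3, 0.5 or 0.8; *cE* assumed 0.9; 200,000 simulated trials per setting.

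| Assumed *cC* | Ratio 0.9 / *cC* | Trials where the exercise proportion exceeds the control proportion |
|---|---|---|
| 0.9 | 1.00 | 44.5% to 46.1% |
| 0.7 | 1.29 | 63.7% to 82.4% |
| 0.5 | 1.80 | 80.3% to 97.6% |
| 0.3 | 3.00 | 92.9% to 99.9% |

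As an example, take a true probability of 0.5 with capture of 0.9 against 0.5. The expected numbers with a recorded event are then 15 × 0.5 × 0.9 = 6.75 per 15 exercise patients and 15 × 0.5 × 0.5 = 3.75 per 15 controls.

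The direction follows whenever control capture is lower. The size is set entirely by the assumed rates, and the effect vanishes when capture is equal.

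**The case against.** The case on the other side has four main parts.

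- **The link to adverse events is not stated.** The only use the article gives for the checklist is to adapt the session. It reads as a safety check for supervised exercise, which has no counterpart in a booklet-based arm. Section 2.7 does not mention it. This stands, and it rules out saying that counts *will* be higher under exercise, as a reader might infer. A route does exist in the exercise arms: severe answers are discussed with study staff, and section 2.7 wants all adverse events reported. No such interim route is described for controls.
- **Controls are asked about symptoms.** They complete the symptom scales at baseline and at the end. A reader might infer that controls are never asked; that is wrong. But two outcome assessments do not replace event capture in between.
- **The article condenses a fuller protocol.** An interim query for controls may be described there. This is why the point says only that none is described. The restriction of the checklist to the exercise groups, however, is written into the text and is not a gap in it.
- **No between-arm analysis of adverse events is planned.** They are not a listed outcome, section 2.10 names no such comparison, and the primary endpoint is feasibility within RE + PS. This stands and limits the point to descriptive tables by arm.

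It is also fair that a self-completed form will not match one completed around a live session, and that the discussion section itself names numerous questionnaires as an attrition risk.

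**Conclusion.** The point holds in a limited form. Between baseline and the end of the intervention, structured symptom elicitation is unequal by stated design: up to 48 checklists per exercise patient, and no interim symptom query described for a control. In an open-label trial that grades adverse events in all arms, a by-arm reading may therefore be inflated against exercise by differential ascertainment, provided that session-elicited symptoms enter the adverse-event record.

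The size cannot be known from the article. Under an assumed 95% capture when elicited, the ratio runs from 1.0 at equal capture, through 1.2 at 80%, to 2.4 at 40% in controls. These figures illustrate the mechanism and do not predict a result. The feasibility endpoint is not affected; the interpretation of safety is.

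**What to change.** 1. State whether checklist answers count as adverse events, and record for each event how it was found.
2. Add the same checklist to the weekly record that controls already return.
3. Base any by-arm adverse-event table on one matched weekly checklist per patient in every arm (at most 16 per patient) plus medical-record events. Fix in advance which session's checklist is used in the exercise arms, and obtain it also in weeks when sessions are missed, since section 2.6.1.1 names illness as a reason for missing them. Report all other session-elicited events in the exercise arms separately.
4. For the period before the change, compare arms on medical-record events only, in all arms and not just in controls. Section 2.7 also sends study-reported events to the medical record, so those that entered it through a session should be identified and set apart.

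How a severe answer from a control is acted on is a clinical matter for the investigators, and none is proposed here.

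**Cost.** A few minutes per control patient per week and one more form. Some difference between a self-completed form and one completed around a live session will remain and should be stated as a limitation. Section 2.8 reports 19 patients as having completed the intervention, so at most 45 − 19 = 26 could benefit as of the article. The same section gives 18 as consented, which does not fit with 19 completed if both are running totals, so the exact number is unclear.
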